## Baseline

Confirmation of parent’s written consent and child verbal assent is required before any baseline assessment can be carried out in schools. The following measures will be administered in the school by the research staff:

Teacher: Conners Teacher Ratings

Attendance over past term (days missed due to illness)

Child: Standardised Reading test

Working memory digit span test

Fingerprick blood measures to assess compliance

At this point assessment measures will be scored by researchers. Children who meet inclusion criteria will be identified and randomization will be performed by telephone.

The following measures will be collected from parents using Freepost mail services and chased up with telephone calls or visits as required.

Parent: Conners Parent Ratings

Health questionnaire

Demographics

## Bi-weekly

Parents will be telephoned to check on any absences their child may have had from school, due to illness, once a fortnight. Details will be logged about any such illnesses, for example upper respiratory illness (nose and throat), lower respiratory illness (lungs, chest), ear infection, vomiting, diarrhea, rash or ectopy, food allergy, asthma, fever, lower GI (gastritis).

## Post-intervention

Teacher: Conners Teacher Ratings

Attendance over past term (days missed due to illness)

Prediction of treatment group

Child: Reading test age

Working memory digit span test

Fingerprick blood measures to assess compliance

Prediction of treatment group

The following measures will be collected from parents using Freepost mail services and chased up with telephone calls or visits as required.

Parent: Conners Parent Ratings

Prediction of treatment group

Health questionnaire

Barkley Side Effects Rating Scale (SERS) (Barkley, 1990)

A final telephone call will be made to parents to check on any absences their child may have had from school, due to illness. Details will be logged about any such illnesses

Participants in both stages of the study will be given a 3 month supply of DHA Omega-3 (Life’s DHA, provided by DSM Nutritional Products) as a token of thanks for their participation in the study.

In due course, the parents of all participating children will also receive details of the overall study results, as will all participating schools.

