# STUDY DESIGN

## Design

This is a randomized controlled trial of DHA Omega-3 versus placebo for 16 weeks (fixed dose, parallel group double blind study).

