## Secondary Endpoints

1. To assess whether supplementation with DHA Omega-3 (600 mg/day) for 16 weeks improves teacher reported behaviour.

2. To assess whether levels of DHA Omega-3 or related fatty acids (assessed objectively via a pinprick blood sample) predict their learning or behaviour.

3. To assess whether any changes in behaviour or cognitive performance are associated with changes in objective measures of blood fatty acid status.

4. To assess whether DHA Omega-3 influences health and/or school attendance

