## Enrolment/ Baseline Assessments

The following baseline measures will be obtained on participating children:

1. Teacher: Conners Teacher Ratings (CTRS-L) (Conners 1997) Attendance at school over previous term
2. Parent: Conners Parent Ratings (CPRS-L) (Conners 1997) Demographics Health questionnaire
3. Child: Word reading and Recall of digits from the British Ability Scales – BAS 3 (Elliot, 2011) and BAS II (Elliott, 1997) Fingerprick blood measures to assess fatty acid status and compliance

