# STUDY TREATMENTS

The study is a simple parallel group randomised double-blind controlled trial comparing the effects of active supplementation with DHA Omega-3 at a fixed dose (600mg DHA Omega-3 per day) versus taste and colour-matched corn/soy placebo. DHA Omega-3 or placebo supplements will be supplied in numbered bottles to be delivered once daily to participating children over 16 weeks by teachers (Monday – Friday) and by parents/caregivers at weekends and during school holidays.

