## Study Schedule

The study will run for 36 months: September 2012 to August 2015. It is anticipated that recruitment will be carried out between September 2012 and January 2015.

NB: The exact study schedule will be planned in detail with participating schools according to term length and any school activities which could interfere with testing sessions (such as examination, sporting or other activities).

Data analysis and write up will be conducted between April 2015 and August 2015.

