### Attendance

Attendance will be measured by way of school records pre and post-intervention. Parents will also be contacted fortnightly in order to establish any absences and the nature of any illnesses during the course of trial. We will make a distinction between absences due to illness and those due to, for example, holidays during term-time.

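### The school-record attendance measure looks back over a school term, a window that is undefined and not tied to the 16 weeks of treatment

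*Protocol*

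**What the plan says.** The fourth item under Secondary Endpoints reads "To assess whether DHA Omega-3 influences health and/or school attendance". The Design section states "This is a randomized controlled trial of DHA Omega-3 versus placebo for 16 weeks", and Study Treatments has the supplement "to be delivered once daily to participating children over 16 weeks", given "by teachers (Monday – Friday) and by parents/caregivers at weekends and during school holidays". The treatment window can therefore cross from one term into the next.

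The protocol takes attendance from two sources.

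- **School records.** Under Enrolment/Baseline Assessments the teacher item is "Attendance at school over previous term". The Baseline section words it as the past term, and so does the Post-intervention section: "Attendance over past term (days missed due to illness". The Attendance section adds only "Attendance will be measured by way of school records pre and post-intervention". The assessment schedule table has no attendance row.
- **Parents.** Fortnightly telephone calls during the trial, and a final call at post-intervention, log absences due to illness.

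On timing, Study Schedule says "The exact study schedule will be planned in detail with participating schools according to term length". It gives no term dates, and no section links the term in the school item to the dates of dosing.

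**The concern.** The endpoint concerns what happens during 16 weeks of supplementation, but the school item returns a total for a calendar term. A child assessed after 16 weeks may be in a later term from the one in which capsules began. If the school reports the last completed term, the total can include weeks before the first capsule and omit treated weeks in the current term. If it reports the current term to date, every counted week is treated, but earlier treated weeks are lost. Different schools could choose different readings.

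This is fixed at data collection. Once a school has returned a single term total, no later analysis plan can separate treated from untreated days. The item also asks for days missed without the number of days the school was open to the child, so children observed for different lengths of time cannot be put on a common scale. At stake is how far the school-record half of an outcome that the protocol itself calls important can be interpreted.

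**Working it through.** **The plan's own figure.** 16 weeks × 7 = 112 days, which agrees with the post-intervention column of the schedule table (Day 112 ± 2).

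**Assumed inputs, because the protocol gives no term or start dates.** Three terms of 15, 12 and 14 calendar weeks, each with a one-week half-term, giving 14, 11 and 13 teaching weeks. Holidays of 2, 2 and 7 weeks bring the year to 15 + 12 + 14 + 2 + 2 + 7 = 52 weeks. Treatment may start in any school week. The post-intervention assessment falls in the week after the sixteenth, and a start is kept only if that is a school week.

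**Formulas, for each start week.**
- Coverage = treated school weeks inside the record ÷ all treated school weeks.
- Share outside treatment = 1 − (treated school weeks inside the record ÷ school weeks in the record).

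**Two single cases.**
- Start in the second week of the 15-week term: 13 treated school weeks, all in that term. Last completed term: coverage 13/13 = 100%, outside 1/14 = 7%. Current term to date: 0/13 = 0%.
- Start in the thirteenth week of the same term: 13 treated school weeks, 3 of them in that term. Last completed term: coverage 3/13 = 23%, outside 11/14 = 79%. Current term to date: 10/13 = 77%, none outside.

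**Averages over eligible start weeks.**

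| Start pattern | Reading of the term | Mean coverage of treated school weeks (range) | Mean share of record outside treatment |
|---|---|---|---|
| Evenly spread | Last completed | about 55% (8–100%) | about 49% |
| Evenly spread | Current to date | about 45% (0–92%) | 0% |
| First four weeks of term | Last completed | about 81% (62–100%) | about 14% |
| First four weeks of term | Current to date | about 19% (0–38%) | 0% |

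On this calendar every treated school week lies in one of the two terms, so the two readings sum to 100% (55 + 45; 81 + 19).

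**Other term lengths.** Two further three-term calendars (14/12/13 and 13/13/13 weeks) gave about 55% and 45% again for even starts, with about 47% outside under the last-completed reading. With equal terms and a 2-week break, a 12-week term under the last-completed reading counts 0 to 10 untreated weeks and misses 2 to 12 treated school weeks (14% to 86%). For terms of 10 to 13 weeks some treated school time is always missed under either reading. For 14 to 16 weeks the loss can be close to zero at favourable start points.

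**Attenuation under the last-completed reading.** If untreated weeks carry no effect, the effect on a daily absence rate is multiplied by 1 − share outside: 1 − 0.49 = 0.51 for even starts, 1 − 0.14 = 0.86 for early-term starts. The matching effective-sample factors are 0.51² = 0.26 and 0.86² = 0.74. Under the current-term reading there is no dilution of this kind. The loss is of observed treated time, in amounts that vary by child.

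**The case against.** The strongest reply is that the school record is only one of two sources. The fortnightly calls and the final call record illness absences across the treatment period. In a randomised, double-blind trial the arms can be compared on those absences without a baseline, since a pre-treatment value adds precision and not validity. All of this stands. A reader might infer that the attendance endpoint as a whole counts untreated days and misses treated ones, so that a null result would be uninterpretable. The protocol does not support that, because the parent log covers the right window.

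A reader might also infer that three quarters of the information on this endpoint is lost, from the factor of 0.26. That figure needs evenly spread starts and the last-completed reading, and it ignores the parent log. The protocol plans the schedule around term length, so starts clustered early in term are at least as plausible, and the factor is then 0.74. Nor is the counting of untreated days certain, since it does not occur if the current term is meant.

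Finally, the source that defines school days missed, and the adjustment model, can properly be left to the statistical analysis plan. The look-back period cannot, because it determines what is collected.

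The parent calls do not remove the point. The school registers and the parent log would cover different dates, so neither can be used to check the other, and a disagreement between them would have no clear meaning. The schedule table lists illness tracking only during and after treatment. A parent health questionnaire is collected at baseline, but its content is not given.

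**Conclusion.** The point holds for the school-record measure. Its window is a term, is open to two readings, and is not tied to the 16 weeks of treatment. On the assumed calendar the last completed term captures on average about 55% to 81% of treated school weeks, with 49% to 14% of the record outside treatment, as starts move from evenly spread to early in term. The current term to date captures about 45% to 19% and adds no untreated weeks. These figures rest on assumed term and start dates and show the range, not an estimate for this trial.

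The same rule applies in both arms, and allocation is minimised by school, so there is no reason to expect bias between arms or a false positive. The consequence is attenuation or reduced precision in one of two sources for a secondary endpoint. The remedy is cheap and must be in place before collection, so the change is worth making.

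**What to change.** In Enrolment/Baseline Assessments, Baseline, Post-intervention and Attendance, replace the term-based item with dated windows taken from the school register:

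- **Treatment window:** days absent through illness and possible school days, from the date of the first capsule to the date of the post-intervention assessment, whether or not capsules were stopped early.
- **Pre-treatment window:** the same two counts over an equal number of school days immediately before randomisation. Both windows can be extracted together at the end, when the number of days is known.

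Use actual recorded dates, since the schedule table's nominal Day 7 for baseline and Day 112 for post-intervention are 112 − 7 = 105 days (15 weeks) apart, not 16 weeks. Compare the arms on absences per possible school day, adjusted for the pre-treatment rate. The statistical analysis plan can then state how the school record and the parent log, now covering the same dates, are to be used together.

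The cost is small. Schools consult the same registers but must extract dated records instead of quoting a term total. No additional visit or test for the child is needed.

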# ASSESSMENTS AND PROCEDURES (2) – Details of measures

## Screening

### Key Stage 1 Reading score

Key Stage tests are nationally standardized assessments taken by all UK children at ages 7, 11 and 14. They encompass five areas: speaking and listening, reading, writing, science and mathematics.

Reading scores from Key Stage 1 tests will be used to screen for children performing in the lowest quintile for their age against national norms at age 7. To be eligible for the study, children must not be judged by teachers to have any other significant learning difficulties.

## Baseline and post-intervention

### Conners Teacher and Parent Ratings (CTRS-L and CPRS-L)

These are standardized highly valid and reliable scales which measure child behaviour over several domains, yielding age-standardised scores for 7 different sub-scales (6 for teacher ratings) and 7 global scales.

These scales have shown significant improvements following fatty acid supplementation in several previous trials, and have been routinely used in medication trials for children with behaviour problems such as ADHD.

### British Ability Scales Word reading

This is an age standardized single word reading test from the British Ability Scales, normed on UK children It is administered to each child individually, taking only a few minutes to complete.

The BAS II version of this measure was used successfully in the Oxford-Durham trial and more recently in the first DOLAB study. This reading assessment is sensitive enough to show significant change over three to four months and will be used for replication purposes.

However, following recent policy changes an alternate-form scale whose content reflects changes in national curricula over the past 15 years has been developed (Elliot, 2011). In light of this, the BAS3 will be used for screening purposes and assessment.

### British Ability Scale (BAS II) Recall of Digits

This is a widely accepted measure of ‘working memory’ from the British Ability Scales. Again it is age standardized and administered at the individual level.

Working memory problems are common to a wide range of different conditions in which Omega-3 supplementation has been found beneficial including dyslexia, dyspraxia, ADHD, depression and age-related cognitive decline. Improvements in working memory are also likely to benefit many different aspects of cognitive performance in the general population.

### Fingerprick blood measures to assess fatty acid status and compliance

A fingerprick blood test will be performed at baseline and at the end of the study for randomized children in order to assess levels of fatty acids including docosahexaenoic acid (DHA Omega-3), arachidonic acid (AA), and eicosapentaenoic acid (EPA Omega-3). These blood samples (labeled by ID No. only) will be collected by way of absorbent paper sealed in a tube and stored in a specific refridgerator before being sent by courier to DSM Nutritional Products in the United States. Both DSM and the investigators will remain blinded to the allocation group until treatment codes are unlocked.

The fatty acid data will be used to verify compliance and to determine the relationship between levels of fatty acids in the blood and specific endpoints.

This blood test will be optional and will appear as a separate item on the consent form, but every effort will be made to maximize participation.

### Prediction of treatment group

The value of this measure is that it tests that the participants have remained blind to their group allocation.

### Side effects scale

Side effects will be measured post-intervention in all randomised children using the Barkley Side Effects Rating Scale (SERS) (Barkley 1990). This scale was designed for use in studies of stimulant medication for ADHD-type symptoms. Based on our own and others’ previous studies, negative side effects are not expected from supplementation with DHA Omega-3, but we are conscious that few studies specifically ask about these effects, so the use of this scale will redress that omission.

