## Early withdrawal

If a participant wishes to withdraw from the study, all unused supplements will be collected and a pill count conducted and recorded. The unused supplements will be returned and retained for the duration of the study; at the end of the study they will be collected for destruction.

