### Withdrawal from Study Intervention

Participants may be withdrawn from the intervention for any of the following reasons:

1. Parent/carer of the child withdraws consent for treatment.
2. Unacceptable adverse effects.
3. Intercurrent illness preventing further participation.
4. Development of serious disease preventing further participation.
5. Any change in the participants’ condition that justifies the discontinuation of participation in the opinion of parent, teacher or clinician.

If a parent/carer wishes to withdraw a child from the intervention, schools will inform the project administrator who should document the reason. The project coordinator will attempt to contact the parent/carer, explain the importance of remaining in the study and being followed-up, and request that data be collected as per the study schedule. Generally, follow-up will continue unless the parent/carer explicitly also withdraws consent for follow-up (see following section).

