# ASSESSMENTS AND PROCEDURES (1) - Overview

The following assessments and procedures schedule will be will be followed during the course of the study.

Assessment and procedures Schedule – DOLAB II

| Procedure | Screening | Baseline | Bi-Weekly Contact | Post-  intervention |
| --- | --- | --- | --- | --- |
|  |  | Day 7 +/- 2 d |  | Day 112 +/- 2d |
| Informed Consent | X |  |  |  |
| Prior & Concomitant Medications | X | X |  | X |
| Inclusion/Exclusion | X |  |  |  |
| Finger Prick (optional) |  | X |  | X |
| BAS 3 Reading Test (C) |  | X |  | X |
| BAS II Reading Test (C) |  | X |  | X |
| BAS II Working Memory Digit Span (C) |  | X |  | X |
| Conners Teacher Ratings (T) |  | X |  | X |
| Connors Parent Ratings (P) |  | X |  | X |
| Demographics (P) |  | X |  |  |
| Randomisation |  | X |  |  |
| Prediction Test Group (T, C, P) |  |  |  | X |
| Barkley Side Effects Rating Scale |  |  |  | X |
| Adverse Events |  |  | X | X |
| Capsule Compliance |  |  | X | X |
| Illness Tracking Questions |  |  | X | X |

Recruitment will be carried out over two years. There will be two assessment points for children: i) screening/baseline, and ii) post-intervention for children who are randomized to treatment.

This section will outline the overall study schedule, the measures that will be administered at each of the assessment points (and by whom), how they will be performed and what will be done with these data.

The following section will provide further details of each of the assessments used.

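### The side-effects scale is given once, at Day 112, with no rating when a child stops capsules and none before treatment, so its between-arm comparison can understate side effects that lead to stopping

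*Protocol*

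**What the plan says.** All references are to the protocol.

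- **Timing of the scale.** Side effects scale: "Side effects will be measured post-intervention in all randomised children using the Barkley Side Effects Rating Scale (SERS) (Barkley 1990". The table in Assessments and Procedures (1) – Overview has one mark for it, in the last column, Day 112 ± 2 days: "Barkley Side Effects Rating Scale | | | | X". The Post-intervention section lists it among the parent forms. The Baseline section does not.
- **Purpose.** The same section says that "few studies specifically ask about these effects, so the use of this scale will redress that omission".
- **Stopping capsules.** Withdrawal from Study Intervention lists "Unacceptable adverse effects" as a reason. The project administrator should record the reason, the coordinator tries to contact the parent, and data are requested on the normal schedule.
- **At withdrawal.** Early withdrawal: "If a participant wishes to withdraw from the study, all unused supplements will be collected and a pill count conducted and recorded". The only other step it names is the return and storage of supplements. Participant Transfer and Withdrawal also asks for an end-of-study evaluation, without giving its timing or content.
- **Full withdrawal.** Withdrawal from Study Completely allows parents to leave without giving a reason, and uses data only up to that point.
- **Other harm data.** The schedule table ticks adverse events at the fortnightly contact and post-intervention. Adverse Event Collection says that parents are asked about adverse events in the fortnightly call.

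**The concern.** The children who tolerate the capsules least are the likeliest to stop. Under this schedule they are rated on the SERS only after a gap off capsules, or not at all. If their complaints have gone by then and the form does not reach back, they count as unaffected. If they have left, they drop out of the comparison. Either way the SERS loses cases that are related to treatment, and its between-arm comparison moves towards no difference.

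At stake is the item-by-item enquiry about side effects that the protocol says earlier studies lacked. A reassuring SERS result would be weaker evidence than it appears. This is a matter of data collection: no analysis plan can recover an on-treatment rating that was never taken.

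A smaller matter is the missing pre-treatment rating. Complaints already present cannot be separated from new ones, so the rate in either arm is not a treatment-emergent rate.

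**Working it through.** The plan states no figure for this point, so there is none to reproduce. The check has a textual part and an illustration.

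**1. Gap between stopping and rating.** "This is a randomized controlled trial of DHA Omega-3 versus placebo for 16 weeks", and the SERS falls at the end of those 16 weeks. Gap = 16 − week of stopping.

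| Week of stopping | Weeks off capsules at the SERS |
|---|---|
| 2 | 16 − 2 = 14 |
| 4 | 12 |
| 8 | 8 |
| 12 | 4 |
| 14 | 2 |

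This applies to a child who stays in follow-up. A child withdrawn completely has no SERS.

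**2. Effect on the comparison (illustration).** The 199 per arm comes from Sample Size. Everything else is assumed, because the protocol gives no side-effect rates, no stopping rates, no SERS recall period and no method of analysing the SERS. Let p0 and p1 be the true proportions with a side effect on placebo and active, and s the share of the excess active cases (p1 − p0) who stop.

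- Rated symptom-free at Day 112: observed active rate a = p1 − s(p1 − p0), still out of 199.
- Missing at Day 112: observed active rate b = a / (1 − s(p1 − p0)), with active n = 199 × (1 − s(p1 − p0)).
- Power, two-sided 0.05, for n per arm and observed active rate a: Φ{[(a − p0) − 1.96√(2p̄(1 − p̄)/n)] / √[(p0(1 − p0) + a(1 − a))/n]}, where p̄ is the mean of p0 and a. The missing case uses the same form with unequal n.

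Worked case, p0 = 0.10, p1 = 0.20, s = 0.25: a = 0.20 − 0.25 × 0.10 = 0.175 and p̄ = 0.1375. The null standard error is √(2 × 0.1375 × 0.8625/199) = 0.0345, and the alternative is √((0.09 + 0.1444)/199) = 0.0343. Power = Φ{(0.075 − 0.0677)/0.0343} = Φ(0.21) = 58.5%.

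| p0, p1 | s | Active rate if rated symptom-free | Power | Active rate if missing | Power |
|---|---|---|---|---|---|
| 10%, 20% | 0 | 20.0% | 80.0% | 20.0% | 80.0% |
| | 10% | 19.0% | 72.4% | 19.2% | 73.8% |
| | 25% | 17.5% | 58.5% | 17.9% | 62.4% |
| | 50% | 15.0% | 32.5% | 15.8% | 40.0% |
| 5%, 10% | 0 | 10.0% | 47.3% | 10.0% | 47.3% |
| | 10% | 9.5% | 40.9% | 9.6% | 41.5% |
| | 25% | 8.75% | 31.5% | 8.9% | 32.7% |
| | 50% | 7.5% | 17.6% | 7.7% | 19.4% |

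At 10% v 20% there are 0.10 × 199 ≈ 20 excess cases, so s = 10%, 25% and 50% mean about 2, 5 and 10 children.

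**3. Does this need every stopper to be in the active arm?** No. If the same share s of affected children in *both* arms stops and is rated symptom-free, the observed difference is (1 − s)p1 − (1 − s)p0 = (1 − s)(p1 − p0). At s = 0.25 that is 15.0% − 7.5% = 7.5 points, the same difference as 17.5% − 10.0%. It shrinks but does not change sign.

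**4. Baseline rating.** If the SERS were analysed as a continuous score adjusted for baseline, variance would fall by the square of the baseline correlation r. For an assumed r of 0.4 to 0.6 that is 16% to 36%. This does not carry over to the proportions above.

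**The case against.** The strongest reply is that the SERS is not the only harm measure. A reader might infer that the schedule hides the harm altogether. The documents do not support that: parents are asked about adverse events every fortnight, illnesses such as vomiting, diarrhoea and rash are logged, and the reason for stopping should be recorded. This part of the reply stands. What it does not supply is the structured enquiry. The call is built around illness absences, with a general adverse event question added, and parents who withdraw fully need give no reason.

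Other replies, and what stands of each:

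- **Recall.** The SERS recall period is not stated, so a rating at Day 112 might still report earlier effects. That stands: the bias is possible, not established.
- **End-of-study evaluation.** It could be read as taking place at withdrawal. That is an open ambiguity. The text does not say that it includes the SERS, and Withdrawal from Study Intervention points to the normal schedule.
- **Size.** A reader might infer that the comparison could reverse and show fewer side effects on active. That needs many affected active children to stop and few or no affected placebo children to do so, and nothing in the protocol supports it.
- **Missing data.** The Analysis Plan provides for imputation and best- and worst-case analyses informed by the reasons for missing data. These may help where the SERS is absent. They do not touch a rating that is present but taken weeks off capsules.
- **Baseline.** A reader might infer that the lack of a baseline biases the comparison. It does not: randomisation makes existing complaints comparable in expectation. Nor does the protocol say that the scale is aimed at children like these. It says "This scale was designed for use in studies of stimulant medication for ADHD-type symptoms", while this trial enrols otherwise healthy poor readers.
- **Importance.** The SERS is not among the listed primary or secondary outcomes. That stands and limits the weight of the point.

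**Conclusion.** The point holds for the structured scale only. The SERS is fixed once, at Day 112, with nothing tied to stopping. Children who stop for adverse effects are rated up to about 14 weeks off capsules (for stopping at week 2), or not at all after full withdrawal. The SERS comparison can therefore understate side effects that lead to stopping. The fortnightly question and the recorded reason cover part of the gap, but not item by item.

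The direction, towards no difference, rests on two assumptions: that complaints have faded by Day 112 and are not recalled, or that the affected child is missing; and that the active arm has the excess of side effects. The size cannot be fixed from the protocol. Under the assumed rates it runs from slight (20% observed as 19%) to serious (power below half of its starting value when half of the excess cases stop). The lack of a baseline affects treatment-emergent reporting and precision, not bias between arms. The change is worth making because it is cheap and strengthens what the trial can say about side effects.

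**What to change.** 1. In Early withdrawal, Withdrawal from Study Intervention, the schedule table and Side effects scale, add a SERS at the parent contact that already follows a decision to stop, covering the period on capsules. Also state whether the end-of-study evaluation is this assessment.
2. Use that rating as the child's on-treatment side-effect value, and keep the Day 112 rating as follow-up.
3. Report the number stopping for adverse effects by arm next to the SERS results.
4. Add the SERS to the baseline parent pack, which already holds the Conners, health and demographic forms, and report new or worsened items by arm.

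The cost is one more short form at baseline and one, by phone or post, for each child who stops. Parent forms become slightly longer, and children already enrolled will have no baseline SERS. A parent who withdraws consent completely may still decline the form, so item 3 is needed even with item 1 in place. Nothing here alters treatment or any rule for stopping it.
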